##### Obstacle course

This test of overall fitness includes running 1 m from a marking cone to a transversally positioned bench, jumping over the bench (36 cm high, 28 cm wide), underpass this bench and running back to the marking cone three times in a row as fast as possible. Time was measured in seconds. This test was described by Vogt (1978) [62] and Kunz (1993) [63] as an ideal test for 3- to 6-year old children to test the overall fitness. The bench was constructed according to the German DIN 7909 standard except for the stabilizing bar, which was left out. Each child had two attempts and the faster one was used. Tests were considered invalid according to predefined criteria, i.e. if the performance was obviously submaximal, or the child did a mistake. The intra- and interobserver correlations in the pilot study (n = 14) using Spearman rank correlation analyses were r = 0.99 (p < 0.01) and r = 0.82 (p < 0.01), respectively. Less than 10% of the children had one invalid attempt and none had two invalid attempts.

##### Balance platform

Static postural control was measured in accordance to a standardized protocol [64] on a balance platform (GKS 1000^®^, IMM, Mittweida, Germany). The balance platform consisted of four sensors measuring displacements of the center of pressure (COP) in medio-lateral and anterior-posterior direction. Data acquisition was monitored (40 Hz) for 25 sec [64]. A balance-pad (Airex balance Pad, Airex, Aalen-Ebnat, Germany) was put on the balance platform, increasing the difficulty of the test. Postural sway was collected measuring the displacement of the COP. The smallest total length of two trial was used for further analysis. For experimental testing, children were asked to stand barefoot, with a 2 cm distance between both heels and feet placed in a 30° angle on the balance-pad, where coloured foot prints were placed. Hands were placed on the hips. After a test-stand for five seconds and a break while children descended from the force plate, the two trials were collected. The intraobserver test-retest correlation for the total length between the two attempts in the pilot study (n = 40) using Spearman rank correlation analyses was r = 0.73 (p < 0.0001).

##### Balance beam

According to Keogh (1965) balance beams are a suitable tool for testing dynamic balance in children [65]. In pilot testing we observed that balancing backwards was too difficult for children aged 4- to 6-years but balancing forward on a 3 cm wide balance beam was feasible and discriminated between children with high and low motor skills. We therefore included balancing barefoot forward on a 3 m long and 3 cm wide balance beam. The number of successful steps on the beam were counted until the child's foot touched the floor. Children performed three trials. The mean of the best two trials was calculated and used for further analyses. The intra- and interobserver correlation between the two better attempts in a pilot study (n = 15) using Spearman rank correlation analyses were r = 0.84 (p < 0.01) and r = 0.97 (p < 0.01), respectively.

#### Physical activity

PA was assessed by an accelerometer (MTI/CSA 7164, Actigraph, Shalimar, FL, USA). The accelerometers were constantly worn around the hip over five days at baseline and at the end of the intervention (both summertime) in the INT and in the CON group. The sampling epoch was set at 15 sec. This instrument has been shown to be valid across different activities in 3- to 5-year old children with a Pearson correlation coefficient between VO_2 _(ml/kg per min) and Actigraph counts/15 sec of r = 0.82 [66].

#### Questionnaires

Table 3 gives an overview of the two used questionnaires [67-74]. The reliability of a semi-qualitative food frequency questionnaire was tested in three classes assessing nutritional behaviour and food intake of preschool children of predominantly migrant background ([name] manuscript in preparation). Items were chosen from different food frequency questionnaires [67-69] adapted to the Swiss situation and the age group. This food frequency questionnaire was also filled in for each sibling aged two years or older.

**Table 3 T3:** Overview of the questionnaires:

General Health Questionnaire	Food frequency questionnaire (adapted from [67-69])
• PA and participation in sports clubs of the child and the family [73]	• Nutritional behavior (i.e. if and where (i.e. home, day care) the meals were eaten, eating while watching television, eating alone)
• media use and sleep duration [74] of the child and its siblings	• Intake of 15 different categories of food during the last 4 weeks (subdivided into nutriments)
• General health of the family members	
• Parental height and weight	
• Socioeconomic data (i.e. education, origin, nationality and cultural integration)	
• health-related quality of life (HRQOL)* [70] • presence of a hyperactive behavior with the Strengths and Difficulties Questionnaire (SDQ)** [71]	

* HRQOL was measured by the German version of the PedsQL 4.0TM (Pediatric Quality of Life Inventory) Generic Core Scales (U.S. Copyright Registration No. TXu 856-101) with a parent proxy-report, containing four scales (Physical, Emotional, Social, School) and 23 items. The psychometric properties of the PedsQL 4.0TM justify application in a healthy child population [70]. ** The presence of hyperactive behaviour was evaluated with the Strengths and Difficulties Questionnaire (SDQ) [71]. The parent proxy-form comprised the hyperactivity/inattention scale consisting of five items. Validity has been demonstrated in healthy children and adolescents [72].

#### Cognition tests

To measure attention ability, the *Konzentrations-Handlungsverfahren für Vorschulkinder *(KHV-VK) [75] was applied. Test material consists of 44 cards with familiar pictures, which had to be sorted into four different boxes. Sorting time and error quote allowed quantitative and qualitative statements on attention. The test has been validated in a preschool population and age specific norms are available. Test-retest reliability was r = 0.88 [75].

Spatial working memory ability was measured by a subtest taken from the Intelligence and Development Scales (IDS) [76]. Thereby geometrical forms had to be memorized and identified. Significant correlations to related measures confirmed construct validity (i.e. HAWIK-IV Working memory scale: r = 0.52) and the test-retest reliability was r = 0.48 [77,78].

### Evaluation

All evaluation measures were developed as defined in the CONSORT guidelines [79]. We will evaluate the intervention with regard to primary and secondary outcome measures. We will also perform a process evaluation to assess the appreciation the feasibility and the subjective effectiveness of the program by teachers (questionnaires and semi-qualitative interviews) and parents (questionnaires).

### Data analysis

Baseline comparability of INT and CON schools will be assessed using descriptive statistics and two sample *t *test for continuous and χ^2 ^test for categorical variables. If necessary, variables will be logarithmically transformed before analyses. As a primary prevention program, the intervention was designed to target the entire sample. Effects are expected and intended to occur throughout the entire distribution of adiposity and aerobic fitness in the sample – not just around a defined threshold. Thus, for purposes of establishing the efficacy of this intervention, it is most appropriate to compare the full distributions of BMI and aerobic fitness between INT and CON groups. Therefore, to test the primary hypotheses, accounting for the design with classes as the unit of randomization, mixed linear models will be used, with change in BMI and aerobic fitness as the dependent variable, study arm as the factor of interest and age, sex, language region (German vs. French part of Switzerland) and baseline BMI or aerobic fitness, respectively, as covariates. The same analytic approach will also be used for all secondary outcome variables. Potential interactions of intervention with sex or age will be tested for each outcome. Data will be analyzed according to intention to treat.

With an average class size of 18, we assumed that 13 children per class would participate in both shuttle run-tests (due to non-participation, attrition, moving, sickness on the testing day). A total number of 40 classes would then provide enough power to detect a true intervention effect of half an inter-subject standard deviation at the usual significance level of 0.05 with a probability of 0.9, provided that the standard deviation of the random class effect does not exceed 25% of the inter-subject standard deviation (i.e., corresponding to an intra-class correlation of about 0.06).

The following subgroups will be also investigated: Normal weight and overweight/obese children, children with low baseline fitness, children with migrant background and Swiss children, children of low socioeconomic background.

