### Study Design

Figure 2 shows a flow diagram of the recruited population. It was performed in two (SG & VD) out of 26 Swiss cantons. The German (SG) and the French (VD) parts of Switzerland represent two culturally distinct regions with different school and preschool systems. Classes from SG and VD were therefore separately selected and randomized after agreement of the school directors and the school health services of both cantons. The city of St. Gallen and the Lausanne area were chosen due to a high prevalence (i.e. at least 40%) of children of migrant background. Migrant background was defined as at least one parent born out of Switzerland. The prevalence of 40% was chosen as the school board estimated that in large adjacent areas with a high prevalence of a migrant population, 40–70% of children were of migrant background. For the selection and randomization opaque envelopes were used. For practical reasons, and to reduce an effect of contamination, preschool classes integrated in the same school building were randomized into the same group.

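### The analysis names the class as the unit of randomisation although classes sharing a school building were allocated together; a class-only model then exceeds 5% type I error to the extent that outcomes cluster by building

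*Protocol article*

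**What the plan says.** Two sections of the protocol article describe the allocated unit differently.

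- **Study Design**: for practical reasons and to limit contamination, "preschool classes integrated in the same school building were randomized into the same group".
- **Data analysis, primary models**: "accounting for the design with classes as the unit of randomization, mixed linear models will be used". The listed covariates are age, sex, language region and the baseline value; no building or school term is named. The same approach is to be used for all secondary outcomes.
- **Data analysis, power**: "A total number of 40 classes would then provide enough power". The target is 90% power at alpha 0.05 for a difference of 0.5 between-child SD. One condition is attached, "provided that the standard deviation of the random class effect does not exceed 25% of the inter-subject standard deviation"; the article equates this with an ICC near 0.06. On cluster size, "we assumed that 13 children per class would participate in both shuttle run-tests".

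The text does not say how many buildings the 40 classes came from, how many buildings held more than one class, or how large the building-level variance is. The participant flow chart was not available for this check.

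**The concern.** Where a building holds two or more classes, one allocation decided the arm for all of them. Those classes are not separate randomised units. If their outcomes are correlated beyond what a class effect captures, a model with only a class effect treats them as independent replicates. It then leaves the between-building variance out of the standard error of the arm effect.

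The error runs in one direction only: intervals too narrow and p-values too small. Because one model form serves both primary outcomes and the secondary outcomes, a single misstatement reaches the trial's main inferences.

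This is more than a detail left to a fuller document. The article states the unit of randomisation and bases the model and the power on it, and its own design section says otherwise. The two statements agree only if every building held a single class, and then the same-building rule would have had nothing to act on.

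**Working it through.** **Inputs.** From Data analysis: 40 classes, 13 children per class, effect 0.5 SD, alpha 0.05, class SD at most 0.25 of the inter-subject SD. Assumed here: two-sided alpha, 20 classes per arm (the ratio is not stated; 343 and 312 consenting children suggest about 1:1), equal class sizes, no covariates.

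**1. The plan's own figures.**
- ICC = 0.25² / (1 + 0.25²) = 0.0625 / 1.0625 = 0.059, which agrees with the stated value of about 0.06.
- Variance of a class mean = 0.0625 + 1/13 = 0.1394. SE of the arm difference = √(2 × 0.1394 / 20) = 0.118. Power = Φ(0.5/0.118 − 1.960) = 0.989, or 0.985 with t on 38 df.
- The stated 0.9 is therefore met as a floor; about 12 classes per arm would give 0.90.

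**2. Direction and size of the SE error.** Set the total variance to 1 and the total cluster variance to 0.06, of which *s* lies between buildings. A class mean has variance v = 0.06 + 0.94/13 = 0.1323, and two classes in one building correlate at ρ = s/v. With *b* classes per building:
- true variance of an arm mean = v[1 + (b−1)ρ]/20
- average value that a class-level test estimates = v[1 − (b−1)ρ/19]/20
- SE ratio r = square root of the quotient; approximate true level = 2Φ(−1.960/r)

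| Layout | Building share of cluster variance | ρ | r | Level |
|---|---|---|---|---|
| All pairs | half | 0.227 | 1.114 | 7.9% |
| All pairs | all | 0.453 | 1.220 | 10.8% |
| All fours | half | 0.227 | 1.320 | 13.8% |
| All fours | all | 0.453 | 1.595 | 21.9% |

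A cross-check with the variances taken as known (cluster 0.0625, residual 1), pairs, all of it between buildings: [0.0625/10 + 1/260] / [0.0625/20 + 1/260] = 1.448, an SE factor of √1.448 = 1.20.

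**3. Simulation.** 40,000 null trials per scenario, with a class-mean t test on 38 df standing in for a balanced mixed model that has a class effect only. Rejection rate at nominal 5%, total ICC 0.06:

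| Layout per arm | Share 0 | 1/6 | 1/2 | All |
|---|---|---|---|---|
| 20 single-class buildings | 5.1% | 5.1% | 5.0% | 4.9% |
| 4 pairs + 12 single | 5.1% | 5.4% | 6.0% | 7.2% |
| 10 pairs | 4.9% | 5.8% | 7.8% | 10.6% |
| 3 threes + 4 pairs + 3 single | 5.0% | 6.0% | 8.3% | 12.3% |
| 5 fours | 5.2% | 7.9% | 13.2% | 21.8% |

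A t test on building means stayed between 4.7% and 5.2% throughout.

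**4. A smaller ICC.** By the formula in step 2, all classes paired: ICC 0.03 gives 6.8% (half between buildings) to 8.6% (all); ICC 0.01 gives 5.7% to 6.4%.

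**5. Power when analysed by building.** Put the cluster variance back at 0.0625 (residual 1), with *s* between buildings and c = 0.0625 − s between classes. Variance = 2[s/G + (c + 1/13)/20], where G = 20/b buildings per arm. For pairs with all cluster variance between buildings: 2[0.00625 + 0.003846] = 0.0202, SE 0.142, power Φ(0.5/0.142 − 1.960) = 0.94. Over half to all of the variance:
- pairs: 0.97-0.94 (normal) or 0.95-0.91 (t)
- fours: 0.91-0.79 (normal) or 0.82-0.68 (t)

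**The case against.** The strongest reply is that the harm is conditional and the upper figures need unfavourable assumptions.

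- A reader might infer that standard errors are certainly too small and that both primary tests certainly exceed 5%. The text does not support that. It requires multi-class buildings, which the same-building rule implies but does not count, and appreciable building variance in the baseline-adjusted change, which is nowhere given and may differ between BMI and fitness. **This stands.**
- The SD of 0.25 is a ceiling, and it comes from a power statement built on shuttle-run attendance. Putting all of it between buildings leaves nothing for the class, although classroom teachers delivered most of the lessons. **This stands**; the top of each range is an upper bound for its layout.
- The article does not say that a class intercept is the only random effect, and a fuller plan may specify more. **This stands in part.** The primary model is nevertheless described as reflecting classes as the randomised unit, and a plan faithful to that sentence would inherit the error.
- One might also conclude that degrees of freedom are overstated, or that classes in a building share staff, gym and catchment. No degrees-of-freedom method is given and no such sharing is described, so neither is a finding. The contamination rationale makes correlation within a building plausible but does not measure it.
- Nor does the point show that the trial is underpowered. With every class paired, power by building still meets 0.9.

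**Conclusion.** The contradiction is real: the article names the class as the unit of randomisation, while its design section allocates buildings wherever they hold several classes. The direction of the consequence is also settled. With at least one multi-class building and any positive building variance, a class-only model is anti-conservative.

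The size is not settled. At the plan's ceiling for cluster variance, with 13 children per class and 20 classes per arm, the true level of a nominal 5% test is:
- about 5% with single-class buildings or no building variance
- about 5.4-7% with a few paired classes
- about 6-11% with all classes paired
- higher with larger buildings, up to about 22% in the extreme case of fours with all cluster variance between buildings

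Smaller cluster variance lowers these figures. The conclusion is therefore inflation to the extent that outcomes cluster by building, not inflation of a known amount.

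**What to change.** 1. In Data analysis, name the school building as the unit of randomisation, with a single-class building as its own unit, and bring Study Design and the power statement into line.
2. Fit the primary and secondary models with a random intercept for building and one for class within building, or use an equivalent building-level analysis.
3. Test the arm effect with small-sample degrees of freedom that reflect the number of buildings; Satterthwaite or Kenward-Roger would serve.
4. Report the number of buildings per arm and region, and restate the power at that level. This matters most if buildings held three or more classes.

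The cost is low: a change of wording and one more variance component, with building membership already known from the allocation. Intervals will be somewhat wider. If few buildings hold several classes, the building and class variances may be hard to separate and the building estimate may fall to zero, so the plan should say in advance what is done then, for example a building-level analysis. If every building held one class, the model reduces to the planned one.

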## Background

Obesity is considered to be a global epidemic by the World Health Organization [1]. The marked increase in childhood obesity is alarming and already present in preschool children reaching 26% in 2- to 5-year old children and to 37% in 6- to 11-year old children [2]. In Switzerland there is a prevalence of overweight and obesity of around 20% and 23% in 6- to 12-year old boys and girls [3]. The prevalence of overweight/obesity and of physical inactivity is especially increased in children of low socioeconomic status (SES) [4] and/or children of migrant background [5,6].

Obese children are at increased risk to become obese adults [7,8] and this tracking becomes stronger the closer the child gets to adult status [9]. Yet, overweight preschool children have an over fivefold risk to be overweight at age twelve years compared with normal weight preschoolers [8]. Childhood obesity is already associated with cardiovascular disease risk factors [10-13] as well as other complications [7,8] and is an independent predictor of coronary heart disease in adulthood [14].

The main environmental causes attributed to the enormous increase in body fatness in the last few decades are an increase in energy intake through food and a decrease in energy expenditure through a decrease in physical activity (PA) and/or an increase in sedentary behaviour [15]. One of the most important contributors to sedentary behaviour is media use (TV, PC, game use) [16] which is also related to energy intake [16]. Another postulated factor associated with obesity and insulin resistance is a lack of sleep [17]. Social, cultural and economic factors also influence energy balance.

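### Variation of the effect with baseline BMI and fitness is to be examined only through categories; adding continuous interaction terms would raise power for this secondary question at almost no cost

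*Protocol article*

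**What the plan says.** All the relevant text is in the protocol article, Methods/Design, Data analysis.

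- **Subgroups.** "The following subgroups will be also investigated: Normal weight and overweight/obese children, children with low baseline fitness"; migrant, Swiss and low socioeconomic groups follow in the same sentence. No cut-point is given for fitness, and low fitness is listed without a comparison group.
- **Interactions.** "Potential interactions of intervention with sex or age will be tested for each outcome". Baseline BMI and baseline fitness are not on this list.
- **Main models.** Mixed linear models for change in each primary outcome include "baseline BMI or aerobic fitness, respectively, as covariates". Nothing there suggests that these covariates are categorised.
- **Thresholds.** "Effects are expected and intended to occur throughout the entire distribution of adiposity and aerobic fitness in the sample – not just around a defined threshold". The conclusion drawn from this is that "for purposes of establishing the efficacy of this intervention, it is most appropriate to compare the full distributions of BMI and aerobic fitness" between the arms.

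The Background section gives the only figure that bears on the size of the overweight group: "prevalence of overweight and obesity of around 20% and 23% in 6- to 12-year old boys and girls". The trial itself enrols children aged 4 to 6 years.

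**The concern.** The subgroup list shows that the investigators want to know whether the programme works differently in heavier or less fit children. As stated, they will look at this through groups. A split treats all children on one side of the cut as alike, and it makes the answer depend on where the cut falls. For overweight, it probably also leaves a small group on one side. If the effect changes gradually along the baseline range, a comparison of two groups is a weak way to see it, although the full measurements are available. What is at stake is a missed gradient in a secondary analysis. The estimate of the overall intervention effect is not at stake.

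**Working it through.** **The plan's own figure.** The article gives no power or information figure for subgroups. Its one power statement concerns the overall comparison: 40 classes, 13 children each, an effect of 0.5 SD, class SD 0.25, alpha 0.05, power 0.9.

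- Intra-class correlation: 0.0625/1.0625 = 0.059, which matches the stated 0.06.
- Variance of a class mean: 0.0625 + 1/13 = 0.139.
- SE with 20 classes per arm (equal arms assumed): sqrt(2 x 0.139/20) = 0.118.
- Two-sided power: 0.989 by the normal formula, 0.985 by noncentral t with 38 df.

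The stated 0.9 is thus met with room to spare. This does not bear on the present point, except that it supplies N = 40 x 13 = 520.

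**Inputs for the subgroup question**
- From the documents: N = 520 (children expected to complete both shuttle runs) and an overweight share of 20-23% (Background, ages 6 to 12).
- Assumed: equal arms, residual SD 1, normally distributed baseline, linear gradient of 0.2 or 0.25 SD in the intervention effect per SD of baseline, two-sided 0.05.

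**Step 1: information kept by a split.** For a standard normal modifier with share p in the smaller group, the fraction kept is phi(z_p)^2/[p(1-p)].

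| Share p | Kept | Lost |
|---|---|---|
| 0.10 | 0.34 | 66% |
| 0.20 | 0.49 | 51% |
| 0.23 | 0.52 | 48% |
| 0.25 | 0.54 | 46% |
| 0.30 | 0.58 | 42% |
| 1/3 | 0.60 | 40% |
| 0.50 | 0.64 | 36% |

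With mildly right-skewed BMI (lognormal, assumed sigma 0.08 to 0.15), the loss at 20-23% is 43-48%. For BMI the range over both shapes is therefore 43-51%. For fitness, if low means anything from the lowest fifth to the lower half, it is 36-51%.

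**Step 2: power by formula, N = 520**
- Continuous term: SE = sqrt(4/520) = 0.0877. A gradient of 0.2 gives z = 2.28 and power 0.63; 0.25 gives z = 2.85 and power 0.81.
- Split at p = 0.22, p(1-p) = 0.1716: the group means of baseline differ by 1.725 SD, so a gradient of 0.2 gives an expected contrast of 0.2 x 1.725 = 0.345. SE = sqrt(4/520/0.1716) = 0.212, z = 1.63, power 0.37. A gradient of 0.25 gives power 0.53.
- Other cuts, relevant to fitness: at 0.2, power is 0.44 (median), 0.42 (lowest third), 0.39 (lowest quarter) and 0.36 (lowest fifth). At 0.25 it is 0.62, 0.59, 0.55 and 0.51.

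**Step 3: check with clustering.** Trials of 40 classes of 13 with class SD 0.25 and a gradient of 0.25 were simulated, 4,000 per setting. Power was about 0.78 with the continuous term. With a split it was 0.59 (median), 0.56 (p = 0.33), 0.51 (p = 0.25) and 0.47 (p = 0.20). Clustering leaves the gap in place.

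**Step 4: larger N for BMI.** BMI may be available in more children than the shuttle run. With all 655 consented children as an upper limit and a gradient of 0.2, the formula gives 0.73 continuous against 0.45 at a 22% split.

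**The case against.** Five objections carry weight.

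1. **The article says only that subgroups will be investigated, and an unseen analysis plan may add a continuous interaction.** That is possible. But the article does fix the form of the two groupings as categories and does name the interactions to be tested. The point proposes a stronger method than the stated one; it does not ask for missing detail.
2. **A reader might infer that the plan contradicts its own argument against thresholds.** It does not. That argument concerns how the outcomes are compared to establish efficacy, and the primary models follow it by keeping change in BMI and fitness continuous. It says nothing about baseline modifiers. Estimates in normal-weight and overweight children are even one way to show effects across the range.
3. **A reader might treat this as a main question because the trial targets a high-risk population.** The high-risk groups in the article are migrant children and those of low socioeconomic status. Variation by baseline BMI or fitness is not among the objectives or outcomes.
4. **The size of the loss rests on assumptions.** This stands. The gradients have no source in the article, the prevalence comes from older children, and the fitness cut is unknown. Yet under normality and linearity even the most favourable single cut, at the median, loses 36%.
5. **Effects in overweight children are easy to interpret, and a split would do better if the effect truly stepped at the cut.** This also stands. It is the reason to add the continuous terms and not to drop the groups.

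**Conclusion.** The point holds as a modest improvement to a secondary analysis. As the article is written, dependence of the effect on baseline BMI and fitness is to be examined through categories alone. With an approximately linear gradient, that gives up about 43-51% of the information for BMI at a 20-23% overweight share, and about 36-51% for fitness. At N = 520 and a gradient of 0.2 to 0.25 SD per SD, power drops from 0.63-0.81 to 0.37-0.53 for a 22% split. The absolute power figures depend on the assumed gradient and N. The relative loss depends on the shape of the baseline distribution, the linearity of the gradient and the cut. The statement that half the information is lost should not be read as a fact about this trial: it is near the mark for BMI under the stated assumptions and may be too high for fitness.

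**What to change.** In the Data analysis section, add study arm by continuous baseline BMI to the BMI model and study arm by continuous baseline fitness to the fitness model, and name these as the tests of effect modification by baseline. Each baseline measure is planned as a covariate only for its own outcome. If a modifier is also tested on another outcome (for example, baseline fitness on change in BMI), its main effect must enter that model too.

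Check for non-linearity, for example with a quadratic term. Report fitted intervention effects with confidence intervals at fixed baseline percentiles, such as the 10th, 50th and 90th. Keep the planned weight-status and low-fitness estimates alongside for clinical interpretation. The migrant and socioeconomic subgroups need no change.

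The cost is a sentence or two of text and two model terms, with no new data. The downsides are reliance on a roughly linear gradient, which the non-linearity check addresses, and two extra tests to be read as secondary.
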